**Table 2: OSI-774 Dose Level Reductions**

| Starting Dose | First Reduction | Second Reduction |
|---------------|-----------------|------------------|
| 150 mg/day    | 100 mg/day      | 50 mg/day        |

Within 2 weeks following a dose interruption or reduction, study drug-related toxicity must improve by at least one grade and be Grade  $\leq 1$ , or further dose reduction by one level will be required. Dosing may be interrupted for a maximum of 2 weeks if clinically indicated and if the toxicity is not controlled by optimal supportive medication. No more than two dose reductions will be allowed.

**Table 3** outlines study drug dose modification criteria for study drug-related toxicities as well as guidelines for their management.

[figure not shown]

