## 11.0 TOXICITIES/SIDE EFFECTS

NCI Common Toxicity Criteria (CTC): This study will utilize the Common Toxicity Criteria (CTC) version 2.0 for toxicity and Adverse Event reporting. A copy of the CTC version 2.0 can be downloaded from the CTEP home page (<http://ctep.info.nih.gov>). All treatment areas have access to a copy of the CTC version 2.0.

All toxic effects will be managed symptomatically, as indicated. Toxicities will be graded using the NCI Common Toxicity Criteria. Dose adjustments will be made as follows:

Dose reduction or interruption of study drug for adverse events may take place at any time during the study. Toxicity is based on NCI-CTC, Version 2.

Management of Grade 1 or 2 rash should include continuation of study drug at the current dose and symptomatic management. If skin rash persists or worsens over 10–14 days, dose reduction according to Table 2 should be considered. Management of Grade 3 rash should include dose reduction and symptomatic management. When skin toxicity improves by at least one grade level, the dose may be re-escalated as tolerated. In Phase II trials, this approach enabled dose re-escalation for the majority of patients requiring dose reduction for skin toxicity. Patients experiencing Grade 4 skin toxicity should be discontinued from the study.

For Grade 1 or 2 diarrhea, early intervention should include continuation of study drug at the current dose and initiation of loperamide therapy as described in **Table 3**. Persistent Grade 2 diarrhea, despite optimal medical management over 48–72 hours, should be managed by dose reduction according to **Table 2**. Patients should be maintained at the reduced dose without attempt at dose re-escalation. Patients experiencing Grade 3 diarrhea should interrupt study drug until resolution to Grade  $\leq 1$  and restart at a reduced dose according to **Table 2**. Patients experiencing Grade 4 diarrhea should be discontinued from the study.

Patients who experience Grade 3 fatigue should be managed with a dose reduction of 150mg to 100mg. Patients who experience Grade 4 fatigue should be discontinued from study.

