Other serious adverse events or Grade 3 or 4 adverse events considered to be related to study drug should be managed with dose interruption until resolution of the event (Grade  $\leq 1$ ). Other serious adverse events or Grade 3 or 4 adverse events not resolving in 2 weeks will result in patient discontinuation. Patients may be rechallenged with study drug at the same dose level if the criteria for rechallenge are met. If the adverse event recurs after rechallenge, the patient should be withdrawn from the study.

[figure not shown]

Memorial Sloan-Kettering Cancer Center  
IRB Protocol

IRB#: 02-010A(8)

Interstitial lung disease/pneumonitis associated with increasing shortness of breath with exertion or at rest may occur. Patients should be instructed to stop drug immediately if they note a worsening of baseline dyspnea or if they develop dyspnea while taking Tarceva. The attending physician should be instructed to immediately start steroids (1 mg/kg) once an infectious etiology has been satisfactorily excluded and to continue steroid treatment for several weeks with a gradual taper as appropriate to maintain optimal pulmonary function.

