| Rash                      |                                                                      |                                                                                                                                                                                                        |
| Grade 1                          | None                                                                 | Any of the following: minocycline a , topical tetracycline, topical clindamycin, topical silver sulfadiazine, diphenhydramine, oral prednisone (short course) at discretion of investigator |
| Grade 2                          | None                                                                 | Manage as described above                                                                                                                                                                              |
| Grade 3 (or intolerable Grade 2) | Dose reduction; dose can be re-escalated when rash is Grade $\leq 2$ | Manage as described above                                                                                                                                                                              |
| Grade 4                          | Discontinue study                                                    | Manage as described above                                                                                                                                                                              |

a Recommended dose: 200 mg po bid (loading dose) followed by 100 mg po bid for 7–10 days.

Investigators are required to report any **SERIOUS** adverse event that may be expected or unexpected, as defined below, and reasonably or probably regarded as caused by investigational product occurring within a protocol-defined period of treatment and post-treatment follow-up.

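### Section 11 gives incompatible dose instructions at two weeks: re-escalate or reduce for rash at Grade 2, and discontinue or reduce for other unresolved drug-related Grade 3 or 4 events

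*Protocol*

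**What the plan says.** Section 11.0 sets dose-modification rules in three places: the running text, the paragraph under Table 2, and Table 3.

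- **Rash, running text.** Grade 3 rash is to be managed with dose reduction. Then: "When skin toxicity improves by at least one grade level, the dose may be re-escalated as tolerated".
- **Rash, Table 3.** For Grade 3 rash, or Grade 2 rash that the patient cannot tolerate: "Dose reduction; dose can be re-escalated when rash is Grade" 2 or lower.
- **Any related toxicity, paragraph under Table 2.** Within two weeks of an interruption or reduction, "study drug-related toxicity must improve by at least one grade and be Grade" 1 or lower, "or further dose reduction by one level will be required". The same paragraph adds: "Dosing may be interrupted for a maximum of 2 weeks", subject to conditions, and caps the number of reductions at two.
- **Other events, running text.** Serious or Grade 3 or 4 events considered drug-related lead to interruption until Grade 1 or lower. Then: "Other serious adverse events or Grade 3 or 4 adverse events not resolving in 2 weeks will result in patient discontinuation".
- **Diarrhea.** The text begins its reduction rule with "Persistent Grade 2 diarrhea, despite optimal medical management over" 48 to 72 hours. The Grade 2 row of Table 3 lists no dose modification.

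Nothing says which of these rules prevails where they overlap.

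**The concern.** A dose-modification section should lead from a given toxicity state to one action. Here, two states at the two-week point lead to two actions that cannot both be carried out. The trial runs at several institutions, so two investigators could treat like patients differently and each cite Section 11.0 in support. One could also follow one paragraph in good faith and be recorded as deviating from another.

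This is first a matter of patient safety and protocol compliance. It also touches interpretation, because dose received and removal from treatment bear on the toxicity profile, on response and on time to progression. Handling that varies by site makes those results harder to read.

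**Working it through.** The protocol has no statistical figure to reproduce on this point. The check applies each rule to the same patient and compares the results.

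| State at two weeks | Section 11.0 text | Table 3 | Paragraph under Table 2 |
|---|---|---|---|
| A. Grade 3 rash, dose reduced, now Grade 2 | Improved one grade: may re-escalate | Grade 2 or lower: can re-escalate | Not Grade 1 or lower: further reduction required |
| B. Intolerable Grade 2 rash, dose reduced, still Grade 2 | No one-grade improvement: re-escalation condition not met | Grade 2 or lower: can re-escalate | Further reduction required |
| C. Other drug-related Grade 3 event, interrupted, now Grade 2 | Not resolved: discontinue | No row | Further one-level reduction required |
| D. As C, but Grade 1 or lower | Same-dose rechallenge possible | No row | No further reduction |

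**State A** is the clearest conflict: two places permit an increase and the third requires a decrease.

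**State B** exposes a fault inside Table 3. Intolerable Grade 2 rash triggers a reduction, yet it already satisfies that row's condition for re-escalation. The text and the Table 2 paragraph then disagree with the table.

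**State C** has two mandatory outcomes, discontinuation and reduction. The word "or further dose reduction by one level will be required" uses might suggest that an earlier reduction is needed, but the paragraph says it applies after an interruption or a reduction, so an interrupted event is covered.

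**State D** shows no conflict. The problem is therefore confined to toxicity still above Grade 1 at two weeks.

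**How many patients.** The inputs are in Section 3.0 (phase II findings, Study 248-1007) and Section 17.0 (possible toxicities).

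- Study 248-1007: Grade 3 rash in 4% of patients, or 4 per 100.
- Same study: one transient dose reduction for skin toxicity among 56 patients; 1/56 = 1.8%, or about 2 per 100.
- Three phase II trials: severe rash in about 2% to 10%, or 2 to 10 per 100. At the initial 50 patients this is 0.02 × 50 = 1 to 0.10 × 50 = 5.

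These figures count patients who could enter State A. Only those whose rash is at Grade 2 two weeks after the reduction meet the conflict, and the protocol gives no figure for that fraction. It also gives none for intolerable Grade 2 rash (State B), or for other Grade 3 or 4 events unresolved at two weeks (State C).

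**The case against.** **The rash permission is optional.** Re-escalation is allowed, not ordered, so a site that never uses the permission at two weeks and applies the Table 2 paragraph breaches nothing. That is true, but it empties the permission at that point for the case it describes, a Grade 3 rash improved to Grade 2. A site that does use it breaches a mandatory rule.

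**Specific rules override general ones.** The text cites Table 2 by name only for rash and diarrhea, and the rule for other events has no reduction step. One can read that rule as governing other events, and the rash rules as exceptions to the two-week rule. These readings are reasonable, and they make State C less clear-cut than State A. They remain the reader's inference: the Table 2 paragraph speaks of drug-related toxicity without exception.

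**Stronger readings that the protocol does not support.**

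- A reader might infer that one patient could be re-escalated, reduced or discontinued for the same state. The conflicts come as two pairs. All three actions meet on a rash patient only if the opening word of "Other serious adverse events or Grade 3 or 4 adverse events not resolving in 2 weeks will result in patient discontinuation" does not limit the Grade 3 or 4 phrase. Since that sentence follows separate rash, diarrhea and fatigue paragraphs, the natural reading excludes rash.
- A reader might see a third contradiction in Grade 2 diarrhea. The text sets out a sequence: continue with loperamide, then reduce if Grade 2 persists. Table 3 matches the first step and omits the second. That is an incomplete table.
- A reader might count the rechallenge wording, "Patients may be rechallenged with study drug at the same dose level if the criteria for rechallenge are met", or the pneumonitis paragraph as further conflicts. No labelled list of rechallenge criteria appears, but the preceding sentences offer a plausible one (resolution within two weeks). The pneumonitis paragraph does not say whether rechallenge applies. Both are omissions.

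**Conclusion.** The point holds for two conflicts: re-escalation against mandatory reduction for rash at Grade 2 at two weeks, together with the Table 3 fault for intolerable Grade 2 rash; and discontinuation against reduction for other drug-related Grade 3 or 4 events unresolved at two weeks. The first is plain on the text. The second rests on the Table 2 paragraph meaning what it says about all drug-related toxicity.

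The number affected is probably small: for the rash conflict, a few to about 10 per 100 patients at most. This assumes that rash here resembles the cited phase II trials and that dose reductions for intolerable Grade 2 rash are as rare as the single skin-toxicity reduction in 56 patients suggests. The number for other events cannot be sized from the protocol.

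A reader might add the 29% moderate and 4% severe rash in Study 248-1007 and conclude that 33 of 100 patients are exposed. The protocol does not support that. Under Table 3 ordinary Grade 2 rash brings no dose change, and the text only asks that reduction be considered if rash persists or worsens. The same study had one skin-toxicity reduction in 56 patients, and Section 17.0 says none of its Grade 3 rashes required one.

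Nor does the point alter the sample size or the response rule in Section 14.0, and with a single arm there is no between-arm bias. It should be corrected because incompatible dosing instructions in a multi-site trial are a safety and compliance problem even when few patients meet them.

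**What to change.** Reconcile the Section 11.0 text on rash and on other adverse events, the paragraph under Table 2, and the rash rows of Table 3, so that each toxicity state at two weeks leads to one action. Alternatively, state which rule takes precedence. The reconciliation should cover rash at Grade 2 after a reduction for Grade 3, rash reduced for intolerable Grade 2, and other drug-related Grade 3 or 4 events not resolved to Grade 1 or lower.

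In the same amendment, align the Grade 2 diarrhea row of Table 3 with the text on persistent Grade 2 diarrhea. It would also be convenient to spell out the rechallenge criteria and say whether they cover pneumonitis.

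The clinical team must choose the rules; none is proposed here. The cost is a wording amendment to Section 11.0 and Table 3 and its notification to the sites. No change to sample size, endpoints or analysis follows.

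### Section 11.0 gives opposite dose instructions for rash that is a tolerable Grade 2 two weeks after a dose reduction, and states no precedence

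*Protocol*

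**What the plan says.** Three places in Protocol section 11.0 govern the dose after a reduction for rash.

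- **Sentence below Table 2.** Within two weeks of an interruption or reduction, "study drug-related toxicity must improve by at least one grade and be Grade" 1 or lower, "or further dose reduction by one level will be required". Both conditions must be met, and no toxicity is excepted. The same paragraph adds: "No more than two dose reductions will be allowed". Table 2 sets the levels at 150, 100 and 50 mg/day.
- **Rash text.** "Management of Grade 3 rash should include dose reduction and symptomatic management". Then: "When skin toxicity improves by at least one grade level, the dose may be re-escalated as tolerated". The text supports this from Phase II experience, where "this approach enabled dose re-escalation for the majority of patients requiring dose reduction for skin toxicity".
- **Table 3, rash rows.** For Grade 3 or intolerable Grade 2 rash: "Dose reduction; dose can be re-escalated when rash is Grade" 2 or lower. For Grade 2 rash in general, the dose change is listed as none.

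A fourth rule, for other serious or Grade 3 or 4 drug-related events, calls for interruption until Grade 1 or lower, and says that such "adverse events not resolving in 2 weeks will result in patient discontinuation".

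**The concern.** The two-week sentence is mandatory and general. The rash rules are permissive and specific. They use different thresholds: Grade 1 or lower, a one-grade improvement, and Grade 2 or lower. Between these thresholds lies a rash that has improved to Grade 2 but not to Grade 1. For that patient, section 11.0 both requires a lower dose and permits a higher one, and it does not say which instruction governs.

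Dosing consistency and the individual patient are at stake. Several centers take part, and each could follow section 11.0 and move the same patient's dose in a different direction. Under the mandatory reading, a patient whose rash is improving goes to 50 mg/day and uses the second of the two reductions allowed. Section 3.0 (Human Pharmacokinetic Studies) reports the target concentration of 500 ng/mL as reached at 100 mg and above.

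**Working it through.** The plan gives no figure to reproduce here. The check is to follow each rule for the same patient.

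**Main case: Grade 3 rash at 150 mg, reduced to 100 mg, assessed two weeks later**

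| Rash at two weeks | Sentence below Table 2 | Rash text | Table 3 |
|---|---|---|---|
| Still Grade 3 | 50 mg required | no re-escalation; Grade 3 calls for reduction | no re-escalation; Grade 3 calls for reduction |
| Grade 2, tolerable | improved by one grade but not Grade 1 or lower: **50 mg required** | improved by one grade: **150 mg permitted** | Grade 2 or lower: **150 mg permitted** |
| Grade 1 or lower | no further reduction | 150 mg permitted | 150 mg permitted |

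The rules agree in the first and third rows. They conflict only in the second, where the two possible doses differ by a factor of 150 / 50 = 3.

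**Second case: intolerable Grade 2 rash, reduced to 100 mg, now tolerable Grade 2.** The grade has not changed.
- The sentence below Table 2 requires 50 mg.
- The rash text does not permit re-escalation, because there is no one-grade improvement.
- Table 3 does permit it.

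Table 3's threshold is also met, literally, by a rash that is still intolerable Grade 2, which is the state that called for the reduction.

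**Diarrhea is not affected.** After a reduction for persistent Grade 2 diarrhea, re-escalation is ruled out. After Grade 3 diarrhea, restart requires Grade 1 or lower.

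**Secondary overlap.** For another drug-related serious or Grade 3 or 4 event still unresolved two weeks after interruption, the rule for such events ends treatment. The sentence below Table 2, which expressly covers interruptions, calls only for a one-level reduction.

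**How many patients.** Section 17.0 (Acneiform Rash) gives 4% Grade 3 rash in the Phase II NSCLC trial and about 2% to 10% severe rash across three Phase II trials. Assume that every such rash is reduced, as section 11.0 directs. Expected number reduced = n × rate:

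| Rate | n = 50 | n = 100 |
|---|---|---|
| 4% | 50 × 0.04 = 2 | 100 × 0.04 = 4 |
| 2% | 50 × 0.02 = 1 | 100 × 0.02 = 2 |
| 10% | 50 × 0.10 = 5 | 100 × 0.10 = 10 |

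At each rate these are upper expected counts for the main case, because only patients at Grade 2 two weeks later meet the conflict. The protocol gives no share for that, and no rate for intolerable Grade 2 rash.

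**The case against.** The strongest reply is that a specific rule displaces a general one. Immediately after the two-week sentence, the protocol introduces Table 3 as the source of dose-modification criteria. Table 3 has its own rash rows, the rash text agrees with them for Grade 3 rash that has improved to Grade 2, and the opposite reading would defeat the re-escalation approach that the text endorses. Most investigators would probably read it this way. That is good evidence of intent, but no sentence states the precedence, and it is just as ordinary to let a mandatory instruction override a permissive one.

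A second reply is that re-escalation is optional, so holding at 100 mg is open. Holding does satisfy both rash rules. It does not satisfy the sentence below Table 2, which requires a step down at Grade 2. The separate advice to consider reduction for Grade 1 or 2 rash that persists 10 to 14 days does not reconcile the rules either, since considering a reduction is not being required to make one.

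On the secondary overlap, the word 'further' suggests an earlier reduction, which patients managed by interruption and rechallenged at the same dose have not had. The two-week limit on interruption also fits discontinuation. This limb is therefore weaker, but the sentence does name interruptions.

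Three stronger inferences are not supported:

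- A reader might size the problem from the single skin-related reduction among 56 patients in section 3.0. Section 17.0 says that no Grade 3 rash in that study required reduction, so that patient does not count toward the Grade 3 case.
- A reader might conclude that 50 mg/day is ineffective. It is a permitted level in Table 2, and section 3.0 reports no concentration at 50 mg.
- A reader might see a threat to the response-rate design. None of its figures depends on these rules.

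**Conclusion.** The conflict is real and narrow. It concerns rash that is a tolerable Grade 2 two weeks after a dose reduction. For Grade 3 rash reduced to 100 mg/day, one rule makes 50 mg mandatory while two others permit 150 mg. The overlap for other serious or Grade 3 or 4 events is secondary.

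At the 4% rate, at most about 2 of 50 or 4 of 100 patients would be reduced for Grade 3 rash (1 to 5, or 2 to 10, over the 2% to 10% range), and fewer would be at Grade 2 two weeks later. This assumes that the earlier rates carry over to this population and that every Grade 3 or severe rash is reduced. Sample size and the response-rate decision rules are untouched. The point is a minor correction for dosing consistency and safety.

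**What to change.** Amend section 11.0 as follows.

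1. Begin the two-week sentence below Table 2 with: *Except for rash (governed by Table 3) and for the other serious or Grade 3 or 4 adverse events above (discontinued if not resolved in 2 weeks),*
2. Add: *For rash, if it is still Grade 3 or still intolerable Grade 2 two weeks after a reduction, reduce one further level; if it is tolerable Grade 2 or less, hold or re-escalate one level as tolerated.*
3. In the Table 3 rash cell, change the re-escalation threshold to *tolerable Grade 2 or less*, and align the re-escalation sentence in the rash text to the same criterion.
4. Keep the cap of two reductions.

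The criterion in step 2 should be tolerability and current grade, not a one-grade improvement. Otherwise an intolerable Grade 2 rash that has become tolerable Grade 2 would still be forced down to 50 mg.

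The cost is an opening clause, one added sentence, one table cell and one aligned sentence in an amendment. It adds no visits, tests or patients.

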**Table 3: Dosage Modification Criteria and Guidelines for Management of Study Drug-Related Toxicities**

| Toxicity,
NCI-CTC Grade       | Study Drug Dose
Modification                                      | Guideline for Management                                                                                                                                                                               |
|----------------------------------|----------------------------------------------------------------------|--------------------------------------------------------------------------------------------------------------------------------------------------------------------------------------------------------|
| Diarrhea                  |                                                                      |                                                                                                                                                                                                        |
| Grade 1                          | None                                                                 | Consider loperamide (4 mg at first onset, followed by 2 mg q 2–4 hours until diarrhea free for 12 hours)                                                                                               |
| Grade 2                          | None                                                                 | Loperamide (4 mg at first onset, followed by 2 mg q 2–4 hours until diarrhea free for 12 hours)                                                                                                        |
| Grade 3                          | Interrupt                                                            | Interrupt until resolution to Grade $\leq 1$ , and restart at reduced dose                                                                                                                             |
| Grade 4                          | Discontinue study                                                    |                                                                                                                                                                                                        |
| Rash                      |                                                                      |                                                                                                                                                                                                        |
| Grade 1                          | None                                                                 | Any of the following: minocycline a , topical tetracycline, topical clindamycin, topical silver sulfadiazine, diphenhydramine, oral prednisone (short course) at discretion of investigator |
| Grade 2                          | None                                                                 | Manage as described above                                                                                                                                                                              |
| Grade 3 (or intolerable Grade 2) | Dose reduction; dose can be re-escalated when rash is Grade $\leq 2$ | Manage as described above                                                                                                                                                                              |
| Grade 4                          | Discontinue study                                                    | Manage as described above                                                                                                                                                                              |

a Recommended dose: 200 mg po bid (loading dose) followed by 100 mg po bid for 7–10 days.

Investigators are required to report any **SERIOUS** adverse event that may be expected or unexpected, as defined below, and reasonably or probably regarded as caused by investigational product occurring within a protocol-defined period of treatment and post-treatment follow-up.

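### Section 11.0 gives three rules for dose changes after a rash-related reduction, and they conflict when the rash is at Grade 2

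*Protocol*

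**What the plan says.** Section 11.0 introduces its rules with "Dose adjustments will be made as follows". Three of the provisions that follow decide what happens after the dose has been lowered for rash.

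- **Table 3, rash row.** The row labelled "Grade 3 (or intolerable Grade 2") carries the instruction "Dose reduction; dose can be re-escalated when rash is Grade $\leq 2". The condition is an absolute grade and is the same for both triggers. Ordinary Grade 2 rash has its own row, with no dose change.
- **Section 11.0, rash paragraph.** "When skin toxicity improves by at least one grade level, the dose may be re-escalated as tolerated". This condition is relative to where the patient started. The same paragraph also allows for a reduction below Grade 3: "If skin rash persists or worsens over 10–14 days, dose reduction according to Table 2 should be considered".
- **Paragraph under Table 2.** Within 2 weeks of an interruption or reduction, "study drug-related toxicity must improve by at least one grade and be Grade" 1 or lower, "or further dose reduction by one level will be required". This covers all study-drug-related toxicity and makes no exception for rash. The same paragraph caps reductions at two.

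Nothing in Section 11.0 says which provision takes precedence.

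**The concern.** The three conditions are built differently: an absolute threshold at Grade 2, a relative drop of one grade, and a relative drop combined with an absolute threshold at Grade 1. They can agree only for some combinations of the grade at reduction and the current grade. In the intolerable Grade 2 branch, the grade threshold in Table 3 is satisfied from the start, so it asks for no fall in grade, while the other two provisions do.

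Consistent dosing and patient safety are at stake. Section 15.1 describes registration from five institutions. Two of them could move the same patient's dose in opposite directions and each cite the protocol correctly. Because only two reductions are allowed, a step down that one passage requires and another does not can use up the allowance. Delivered dose and rash-related discontinuation would then vary by site for reasons unrelated to the drug.

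**Working it through.** No sample-size or error-rate formula applies. The check sets the three rules against each combination of grade at reduction (S) and current grade (C).

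- Table 3: re-escalation allowed if C ≤ 2.
- Section 11.0 text: re-escalation allowed if C ≤ S − 1.
- Paragraph under Table 2, at 2 weeks: requirement met if C ≤ S − 1 and C ≤ 1; otherwise one more step down.

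| S | C | Table 3 | Section 11.0 text | Under Table 2 (at 2 weeks) |
|---|---|---|---|---|
| 2 (intolerable) | 2 | may go up (2 ≤ 2) | not met (2 > 1) | must go down |
| 2 (intolerable) | 1 | may go up | may go up | met |
| 3 | 3 | not met | not met | must go down |
| 3 | 2 | may go up (2 ≤ 2) | may go up (2 ≤ 2) | must go down (2 > 1) |
| 3 | 1 | may go up | may go up | met |

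The rules conflict in two rows, both with the current rash at Grade 2.

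1. **Reduced for intolerable Grade 2, still Grade 2.** The three provisions give three different answers. Before the 2 weeks are up, the third has not yet taken effect and the conflict is between Table 3 and the text.
2. **Reduced at Grade 3, now Grade 2.** Table 3 and the text agree with each other, but the paragraph under Table 2 points the other way.

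**Size.** The only observed rate of reduction for skin toxicity in the protocol is in Section 3.0 (Study 248-1007, 150 mg/day): one patient of 56.

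- 1/56 = 1.8%, or about 2 per 100 patients and 1 per 50, across all skin grades.
- One event is imprecise. The exact 95% upper limit solves (1 − p)^56 + 56p(1 − p)^55 = 0.025. At p = 0.0955 the left side is 0.9045^55 × (0.9045 + 56 × 0.0955) = 0.00400 × 6.25 = 0.025, so the limit is about 9.6%. The lower limit is 1 − 0.975^(1/56) = 0.05%.
- Section 17.0 says that no patient with Grade 3 rash in that study needed a reduction. If both statements are right, the one reduction was not made for a Grade 3 rash.

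**The case against.** The strongest reply is that the wording leaves room for judgement. Table 3 grants permission only, and the text adds that re-escalation must be tolerated. Since tolerable Grade 2 rash has its own row with no dose change, an investigator could sensibly read the table as allowing re-escalation once the rash has become tolerable. This reply has force against one stronger reading. A reader might infer that the table makes a reduction and its reversal share one trigger, so that the reduction cancels itself. They do not: reduction needs Grade 2 rash that is also intolerable, and a patient whose rash is still intolerable would fall back into the reduction row. But the table does not state a return to tolerability as a condition. Nor would that reading remove the conflict with the paragraph under Table 2, which turns on grade alone and is mandatory.

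It can also be said that the re-escalation sentence in the text follows directly on the Grade 3 sentence and may belong to it alone. If so, the text is silent on intolerable Grade 2, and the three-way conflict there becomes a two-way one. The Grade 3 conflict is unchanged.

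A further defence is that rash-specific rules override the general paragraph. That would be a reasonable convention, but Section 11.0 does not state it, and Table 3 and the text would still differ in the Grade 2 branch unless the text is confined to Grade 3.

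**Conclusion.** The inconsistency is real and appears on the face of Section 11.0. It affects a patient still at Grade 2 after a reduction for intolerable Grade 2 rash, and a patient reduced at Grade 3 whose rash is now Grade 2. For a rash that has come down to Grade 1, or is still at Grade 3, the provisions are compatible.

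The number of patients is probably small: about 2 per 100 on the protocol's own figure, with an upper limit near 10 per 100. This assumes that the earlier study's reduction rate carries over to this population and these rules. Only some of those patients would reach a conflicting combination of grades.

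A reader might infer a larger number from the 29% of patients with moderate rash in Section 3.0. That would mean assuming that moderate equals Grade 2 and that some share of those rashes is intolerable. The protocol supports neither assumption, and the single observed reduction argues against a high share. A reader might also infer that the response rate or the two-stage rules are compromised; nothing in the protocol shows that.

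**What to change.** Reconcile three places together: the rash paragraph of Section 11.0, the paragraph under Table 2, and the rash row of Table 3. For each grade at which the dose was reduced, the protocol should then give one condition for going up and one for going down, in the same words wherever it appears. If rash is meant to be exempt from the general paragraph under Table 2, that should be stated. Editing the Table 3 row alone is not enough, because the conflict for Grade 3 rash improved to Grade 2 would remain. Which condition is right is a clinical decision for the sponsor.

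The cost is a short wording amendment to one section and notice to the participating institutions. It needs no added patients, visits or procedures.
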